# Aim and outcome measures

The aim is to test effects of using formal kick counting chart in the third trimester of pregnancy in an unselected population. The research questions are:

Does Fetal Movement Counting:

1. Improve the identification of risk pregnancies / pathology?

*Primary outcome measures*: Numbers of identified pathological conditions in pregnancies (fetal growth restriction (FGR), acute caesarean section on fetal indication/non–reactive non-stress test (NST), oligohydramnios, pathologic blood flow in arteria umbilicalis, maternal perception of absent fetal movements for more than 24 hours before admission to hospital, or perinatal death).

*Secondary outcome measures*: Frequency of consultations because of maternal concern, use of resources in evaluation of these pregnancies (NST, ultrasound, Doppler, recurrent consultations), induced or spontaneous start of delivery, mode of birth.

1. Affect the women’s well-being?

*Primary outcome measure*: Maternal concern.

*Secondary outcome measure:* Maternal satisfaction with use of FMC and sense of control in interpretation of signals from own body and child.

1. Stimulate maternal-fetal attachment antepartum?

*Primary outcome measure*: Maternal-fetal attachment.

*Secondary outcome measure:* Health promoting behavior in pregnancy (smoking habits, use of alcohol, attending standard program for antenatal care).

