#### Identification of perinatal risk factors in actual pregnancy

This study is not suited to use primary outcome measures which are frequent used in traditional epidemiological research on these topics. Earlier studies on research on fetal movements and the relevance and significance of FMC, consequently use primary outcomes as perinatal death, fetal growth restriction, severe fetal asphyxia, acute caesarean section, preterm birth and transfer to NICU. However, these “hard” and relatively rare outcomes are not useful for this study, since this study aims to register the mothers’ ability to identify significant changes of fetal activity, i.e. the number of identified pregnancies with a risk condition on basis of the mothers’ interpretation of fetal movements and management if significant changes. Therefore, the primary outcomes in this study are identification of risk pregnancies, e.g. number of consultations where an intervention or further observation was indicated on basis of the mothers’ perception of DFM.

Primary outcome measures – pathology identified according to Norwegian guidelines:

- Fetal growth restriction (FGR) identified by ultrasound prior to birth:
- FGR at birth, unidentified prior to birth
- Acute caesarean section on fetal indication (exclusive protracted delivery)
- Non–reactive non-stress test (NST)
- Oligohydramnios
- Pathologic flow in arteria umbilicalis
- Maternal perception of absent fetal movements for more than 24 hours before admission to hospital:
- Perinatal death

Secondary outcome measures:

- Frequency of consultations because of maternal concern
- Use of resources in evaluation of these pregnancies (NST, ultrasound, Doppler, recurrent consultations)
- Induced or spontaneous start of delivery
- Mode of birth

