## Identification of risk pregnancies

The goal is to increase the accuracy of maternal perception of DFM as a predictor for need of examination or intervention. This will be measured by a compound measure of rates of identification of risk pregnancies related to DFM. Prevalence of risk conditions are estimated from preliminary results of Femina (unpublished) or the Norwegian Birth Register.

| Condition | Prevalence |
| --- | --- |
| Fetal distress: Acute caesarean section on fetal indication (excl protracted birth), non-reactive NST, pathological levels of fetal scap-pH or Apgar5 min ≤ 3 | 8 % |
| Fetal growth restriction < 2.5 centile or pathological Doppler flow in arteria umbilicalis | 5 % |
| Absent fetal movements for more than 24 hours | 0.5 % |
| Intrauterine death | 0.02 % |
| Estimated prevalence of compound measure | 13.52 % |

The goal is a 10% increase of identification of these risk pregnancies, which gives an estimated sample of 538 in each arm of the trial with 80% power and a significance level of 0.05.

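### The composite behind the 13.52% base rate and the 538 per arm in Section 8.1 is not the primary outcome defined in Sections 3 and 4.3

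*Protocol*

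**What the plan says.** Three places in the Protocol describe the primary outcome for the first research question.

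- **Section 3 (Aim and outcome measures)** gives it as "Numbers of identified pathological conditions in pregnancies". The list runs from fetal growth restriction (FGR), acute caesarean section on fetal indication or non-reactive NST, oligohydramnios and abnormal umbilical artery flow to "maternal perception of absent fetal movements for more than 24 hours before admission to hospital, or perinatal death".
- **Section 4.3 (Identification of perinatal risk factors in actual pregnancy)** first equates the measure with the number of pregnancies found to have a risk condition. It then offers as an example the "number of consultations where an intervention or further observation was indicated on basis of the mothers’ perception of DFM". Its bulleted list is close to that of Section 3 but splits FGR in two, the second part being "FGR at birth, unidentified prior to birth". The same subsection says of a group of endpoints that includes perinatal death, FGR and acute caesarean section that "these “hard” and relatively rare outcomes are not useful for this study", and then lists those three as primary.
- **Section 8.1 (Identification of risk pregnancies)** uses a compound rate with four rows: fetal distress 8%, FGR below the 2.5 centile or abnormal umbilical flow 5%, absent movements for over 24 hours 0.5%, and intrauterine death 0.02%. The total is 13.52%. The fetal-distress row includes "non-reactive NST, pathological levels of fetal scap-pH or Apgar5 min ≤ 3". From this and a 10% increase the section derives 538 per arm at 80% power and a significance level of 0.05.

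The Sample section adopts 538 per arm as the trial's preliminary size, to be reassessed after the first part of the inclusion period.

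**The concern.** A base rate is useful for sizing a trial only if it is the rate of the outcome to be analysed. Here the table that produces the rate and the lists that define the outcome differ in what they count. The 538 per arm, which sets the size of the whole trial, is therefore attributed to an outcome that the protocol does not define as primary.

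Two further matters affect what is counted. First, a binomial comparison needs each randomised woman to contribute one yes or no. Counting conditions or consultations lets one woman contribute several times. The protocol itself asks whether counting movements raises the use of health services, so a consultation count could rise in the intervention arm without more women at risk being found. Second, growth restriction missed until birth is something the intervention is meant to reduce, yet it stands among measures whose goal is an increase.

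**Working it through.** **Step 1. Components side by side.**

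| Component | Section 3 | Section 4.3 | Section 8.1 |
| --- | --- | --- | --- |
| Acute caesarean, fetal indication | yes | yes | yes |
| Non-reactive NST | yes | yes | yes |
| Scalp pH | no | no | yes |
| 5-minute Apgar ≤ 3 | no | no | yes |
| Oligohydramnios | yes | yes | no |
| Abnormal umbilical flow | yes | yes | yes |
| FGR | yes, no centile | yes, by national guidelines, no centile stated | yes, below 2.5 centile |
| FGR missed before birth | not listed | yes | not separated |
| Absent movements > 24 h | yes | yes | yes |
| Death | perinatal | perinatal | intrauterine |

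Sections 3 and 4.3 nearly agree. The component conflict is mainly between those two and Section 8.1.

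**Step 2. Unit.** Section 3 counts conditions. Section 4.3 names pregnancies, then consultations as an example. Section 8.1 uses a rate of risk pregnancies.

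**Step 3. Direction of missed FGR.** If FGR found before birth and FGR missed before birth both count, a growth-restricted fetus scores one either way. A case that counting moves from missed to found leaves the total unchanged. Taken alone, the missed item should fall if the intervention works.

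**Step 4. The plan's own base rate.** 8 + 5 + 0.5 + 0.02 = 13.52%, so the sum is correct. It assumes that no woman falls in two rows. With complete overlap the proportion of women affected would be that of the largest row, 8%, so these four rows fix the per-woman rate only to between 8% and 13.52%.

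**Step 5. The plan's own sample size.** With p1 = 0.1352, 1:1 allocation (assumed from the equal arms), two-sided 0.05 and 80% power:

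n = [1.960 √(2p̄(1−p̄)) + 0.842 √(p1(1−p1) + p2(1−p2))]² / (p2 − p1)²

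- 10% relative, p2 = 0.1352 × 1.10 = 0.1487: 10,460 per arm.
- 10 points absolute, p2 = 0.1352 + 0.10 = 0.2352: 236 per arm.

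One-sided tests and continuity correction do not give 538 either (8,239 to 10,607 for the relative reading, 186 to 256 for the absolute). With 538 per arm, two-sided power is about 9% for the relative and about 99% for the absolute reading. At 80% power, 538 detects about 13.5% against 19.9%, a ratio of about 1.47. This failure to reproduce is a separate defect. It matters here only because 538 can be said to be attributed to the Section 8.1 composite, not to follow from it.

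**Step 6. Can the figure be moved to the Section 3 or 4.3 outcome?** No. The Protocol gives no prevalence for oligohydramnios, perinatal death or FGR missed before birth, nor any number of consultations per woman. The 8% row cannot be split to remove scalp pH and Apgar.

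**Step 7. Illustration only, on assumed values.** Take control rates of 10% to 20% and a ratio of 1.464, close to what 538 can detect from 13.52%:

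| Assumed control rate | n per arm for 80% power | Power at 538 per arm |
| --- | --- | --- |
| 10% | 787 | 64% |
| 12% | 637 | 73% |
| 13.52% | 553 | 79% |
| 15% | 488 | 84% |
| 20% | 338 | 94% |

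This shows how sensitive the size is to the base rate. It does not estimate the rate of either definition.

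**The case against.** The strongest reply is that the protocol's intent is clear and its wording merely loose. The lists in Sections 3 and 4.3 are almost the same. Consultations appear only as an example, directly after a phrase that names pregnancies. The background section on maternal ability to identify changes also states the aim as the number of risk pregnancies identified, as does Section 8.1. Consultation frequency because of maternal concern is already secondary. Much of this stands. The unit is probably the pregnancy, and what is needed there is consistent wording, not a change of design.

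Three stronger readings are tempting, and the document does not support them.

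- A reader might infer three mutually incompatible definitions. On components there are essentially two versions, plus the split of FGR in Section 4.3.
- A reader might infer from the eight bullets in Section 4.3 that eight primary tests are planned, with the matching inflation of false positives. The opening of Section 8 speaks of three primary outcomes, which fits one per research question, and Section 8.1 calls the first a compound measure. No passage plans eight tests.
- A reader might infer that Section 8.1 leaves out missed FGR. Its FGR row is not limited to antenatal detection and may cover both kinds.

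It can also be said that aligning the lists would not repair the 538. That is true, but the figure cannot be recalculated properly until the outcome is fixed.

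**Conclusion.** The point holds. The Section 8.1 composite differs from the defined primary outcome by two added components (scalp pH, Apgar), one omitted component (oligohydramnios), a different death endpoint and an FGR cut-off found only there. Section 4.3 also lists a failure of identification among measures of identification. This is a contradiction within current text, not detail left to an analysis plan.

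The effect on base rate and power is unknown and cannot be derived from the document. The range in the last step of the working rests entirely on assumed control rates and an assumed ratio. What is established is that 13.52%, and the 538 attributed to it, do not refer to the outcome defined as primary. Because that figure was adopted as the trial size, the mismatch should be resolved before the planned reassessment of sample size.

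**What to change.** - State one primary outcome for the first research question: a yes/no composite per randomised woman, each woman counted once.
- Give the same closed component list, with any thresholds, in Sections 3, 4.3 and 8.1. Whether scalp pH, Apgar, oligohydramnios, and intrauterine or perinatal death belong in it is for the sponsor to reconcile. The same goes for the FGR cut-off.
- Take FGR missed before birth out of the count of identified risk pregnancies and report it separately.
- Keep the individual components and the consultation counts as secondary.
- Restate the base rate for that composite as a proportion of women, allowing for overlap between rows. Restate the sample size or power, saying whether the 10% is relative or absolute. Give any missing prevalence as an explicit assumption with a range.

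The cost is protocol wording, one revised base-rate table and one recalculation. Prevalences not now in the document must be sourced or assumed. No further data are needed from participants, provided the retained components are recorded in the case notes that are already to be copied.

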## Sample

A total population of singleton, Norwegian-speaking women will be invited after screening ultrasound in pregnancy week 17, exclusive pregnancies with severe anomalies or other cause to consider termination or non-Norwegian speaking/understanding women. Women will be recruited from hospitals not included in existing Femina collaboration. The period of inclusion should be intensive and as short as possible and in a geographical spread area, in order to minimize the potential contamination of information between participants, and to make the conditions for both health professionals and respondents as homogenous as possible.

Sample power analyses based on the preliminary observational study is done to estimate the number of respondents needed. The preliminary estimate with 80% power and a significance level of 0.05, is a total of 538 pregnancies in each arm of the trial. This will be further assessed after evaluation of the first part of the inclusion period.

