# Power analyses

Estimations of sample size needed to preserve the needed power vary widely with the issue being studied. Some examples on how effects of sample size will affect some of the measurements in this study are done by evaluating the effect of the intervention. This is done with the computer program PS Power and Sample Sizes62. The effects of changes is estimated by relative risk for dichotomous variables and means with standard deviations for continuous variables Power analyses only for the three primary outcomes are included here.

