## Maternal concern

The goal is to identify no increase in the level of concern in the intervention group. In the original study with 1207 respondents in the 16 items (0-5) inventory with a 6-point Likert scale, unweighted mean scores across items and standard deviations for the survey in pregnancy week 35 were 1.13 (0.65)59. Detectable changes are estimated to be a change in mean of 0.12, which give an estimated sample of 462 participants in each arm of the trial with 80% power and a significance level of 0.05.

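### The 538 women per arm cannot be derived from a 13.52% base rate and a 10% increase; on the relative-risk scale the protocol names, power is about 10%, not 80%

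*Protocol*

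**What the plan says.** The protocol's section on identification of risk pregnancies (under Power analyses) adds four prevalences, 8%, 5%, 0.5% and 0.02%, to a compound prevalence of 13.52%. It then states: "The goal is a 10% increase of identification of these risk pregnancies, which gives an estimated sample of 538 in each arm", with 80% power and a significance level of 0.05. It does not say whether the 10% is relative or in percentage points, nor whether the test is one- or two-sided.

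The opening of Power analyses gives the scale for this type of outcome: "The effects of changes is estimated by relative risk for dichotomous variables". It names PS Power and Sample Sizes as the software.

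The Sample section takes the number forward as the size of the trial. The preliminary estimate there "is a total of 538 pregnancies in each arm of the trial", to be looked at again after the first part of inclusion. No other trial size is given.

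**The concern.** A 10% relative increase on a base rate of about 13.5% is a difference of less than one and a half percentage points. A trial of roughly 1,100 women cannot detect that reliably, so 538 per arm at 80% power looked far too small. Ten percentage points would be a large difference, and for that 538 looked too many.

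This calculation sets the trial's size: 538 exceeds the 462 and 64 per arm that the protocol gives for its other two primary outcomes. If the relative goal is the intended one, a non-significant result on the first research question would say very little. A reader relying on the stated 80% power could nevertheless take it as evidence that counting does not improve identification.

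**Working it through.** **Inputs**
- Control rate p0 = 0.1352 (8 + 5 + 0.5 + 0.02 = 13.52; the sum is correct and assumes that no woman has two conditions).
- Effect: a 10% increase, scale not labelled in the sentence; relative risk according to the opening of Power analyses.
- Power 80%, alpha 0.05, equal arms.
- Sidedness is not stated; two-sided is assumed. The maternal-concern calculation supports this: "a change in mean of 0.12, which give an estimated sample of 462 participants in each arm of the trial", with SD 0.65, gives 2 × (1.960 + 0.842)² × 0.65² / 0.12² ≈ 461 two-sided. The attachment calculation (difference 5, SD 10.2) gives 66 against 64 stated. Both come close; the 538 is the outlier.

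**Formula** (two proportions, pooled variance under the null, p̄ the mean of p0 and p1)

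n per arm = [1.960 √(2p̄(1−p̄)) + 0.842 √(p0(1−p0) + p1(1−p1))]² / (p1 − p0)²

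**Attempt to reproduce 538**

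1. *Relative reading.* p1 = 0.1352 × 1.10 = 0.14872; difference 0.01352; p̄ = 0.14196. The two square roots are 0.4936 and 0.4935. The bracket is 1.3827, so n = 1.3827² / 0.01352² ≈ 10,460 per arm. With continuity correction it is 10,607; one-sided, 8,239.
2. *Absolute reading.* p1 = 0.2352; difference 0.10; p̄ = 0.1852. The square roots are 0.5494 and 0.5448. The bracket is 1.5353, so n = 1.5353² / 0.10² ≈ 236 per arm. With continuity correction it is about 255; one-sided, 186.
3. *Other variants.* Unpooled variance, an odds ratio of 1.1, decreases instead of increases, and the absolute reading at 90% or 95% power (316 and 390) all miss 538. Inflating the absolute figure for dropout comes near 538 only at a loss of about 55%, and the protocol states no such loss.
4. *Other base rates.* At 80% power, two-sided and without continuity correction, the number needed for a 10-point difference never exceeds about 391 per arm, whatever the base rate. For a risk ratio of 1.10, 538 arises only at a base rate near 73%.

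**Power with 538 per arm**

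Power = Φ[(p1 − p0 − 1.960·SE0) / SE1], where SE0 and SE1 are the two square roots divided by √538.

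- Relative: SE0 = 0.02128 and SE1 = 0.02128. (0.01352 − 0.04171) / 0.02128 = −1.325, which gives 9.3%, or 9.7% counting both tails. One-sided it is about 16%.
- Absolute: SE0 = 0.02368 and SE1 = 0.02349. (0.10 − 0.04642) / 0.02349 = 2.281, which gives 98.9%.

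**What 538 per arm does detect**

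Setting n = 538 and solving for p1 gives 19.9%: risk ratio 0.1988 / 0.1352 = 1.47, or 6.4 points. With continuity correction p1 is 20.1% (risk ratio about 1.49).

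| Reading of the 10% increase | Needed per arm (80%, two-sided) | Power at 538 per arm |
|---|---|---|
| Relative, 13.52% to 14.87% | about 10,460 | about 10% |
| Absolute, 13.52% to 23.52% | about 236 | 98.9% |
| Effect that fits 538: 13.52% to 19.9% | 538 | 80% |

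**The case against.** The arithmetic is not in dispute. The case on the other side concerns what may be concluded from it.

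- *The scale is an inference.* The sentence with the goal does not say relative. Under the absolute reading the trial is oversized, not underpowered. This stands as a condition on the 10% power figure. It does not rescue 538, which is more than twice the absolute requirement, and the only statement on scale in the protocol points to relative risk.
- *Prevalence is not an identification rate.* The table gives prevalences of conditions, while the goal concerns identifying them, and no control-arm identification rate is stated. The table also does not match the outcome lists: they include oligohydramnios, which the table omits, and the table includes scalp pH and Apgar score, which they omit. So the magnitudes depend on taking 13.52% as the control rate. The protocol itself uses it as the base of this calculation. If the conditions overlap, the rate is lower and the relative goal needs still more women (about 14,750 per arm at 10%).
- *The number is preliminary and the calculations are called examples.* True, but it is the only size given and 80% power is claimed for it. A later reassessment has no usable target if the starting effect is undefined.
- *Restating the effect that 538 detects is working backwards.* This is fair: nothing in the protocol shows that a risk ratio of 1.47 is plausible or was the sponsor's aim. The restatement only describes truthfully what the planned size can show.

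**Conclusion.** The concern holds. The stated 538 per arm and 80% power are incompatible with a 13.52% base rate and a 10% increase on either scale, and no standard variant of the calculation closes the gap. On the better-supported relative reading, the size is too small by a factor of about 19 (10,460 / 538) and power is about 10%. On the absolute reading, it is about 2.3 times what is needed (538 / 236).

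That 538 does not follow from the stated inputs is certain. The power figures rest on two assumptions: that 13.52% is the control-arm event rate, and that the test is two-sided at 5%. One-sided testing raises power on the relative reading only to about 16%. The error affects the first of three primary questions; the sizes for the other two reproduce approximately and lie below 538.

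**What to change.** Keep 538 per arm and correct the claim attached to it, in both the Sample section and the section on identification of risk pregnancies:

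- Remove the 10% increase. State that, with a control rate of 13.5%, 538 per arm gives 80% power (two-sided 5%) to detect a rise in the composite to 19.9%, a risk ratio of 1.47.
- State that a 10% relative increase would be detected with only about 10% power.
- State that the result will be reported as a risk ratio with a 95% confidence interval, so that a non-significant result is read against the range of effects it leaves open.

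If the sponsor had another effect in mind, it should instead give the scale and the expected rate in each arm and recompute the size from those.

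The restatement changes protocol wording only and adds no women. Its cost is a less favourable stated effect: the trial can no longer be said to be powered for a 10% increase.

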## Maternal concern

The goal is to identify no increase in the level of concern in the intervention group. In the original study with 1207 respondents in the 16 items (0-5) inventory with a 6-point Likert scale, unweighted mean scores across items and standard deviations for the survey in pregnancy week 35 were 1.13 (0.65)59. Detectable changes are estimated to be a change in mean of 0.12, which give an estimated sample of 462 participants in each arm of the trial with 80% power and a significance level of 0.05.

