## Data analyses

Data handling will be performed in SPSS 14.0. Best suited statistical methods will be chosen in the analyses. Participants will be handled according to the intention-to-treat-principle.

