## Overview over data collection

|  | Survey I | Survey II | Copy of case notes |
| --- | --- | --- | --- |
| Maternal-fetal attachment |  | x |  |
| Mental well-being | x | x |  |
| Maternal depression level | x |  |  |
| Self-efficacy | x |  |  |
| Self-esteem | x |  |  |
| Experiences with FMC to the intervention group |  | x |  |
| Experiences if examined because of DFM |  | x |  |
| Demographic details | x |  | x |
| Obstetric history |  |  | x |
| Planned pregnancy | x |  |  |
| Number of US’s in this pregnancy |  | x |  |
| Known fetal gender | x | x |  |

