# Appendix I: Flowchart data collection

Screening ultrasound

Excluded, mothers:

with multiple pregnancy

with fetal malformations and termination of pregnancy is considered

who not speak/understand Norwegian

Pregnancy week 17-18

Control group – standard antenatal care

Pregnancy week 28

Intervention group starts FMC

Telephone contact

Pregnancy week 29

Pregnancy week 34

Information about the study, invitation to participate and a form for informed consent to fill in

Questionnaire 34-K

Simple randomization

Post partum

Return of the counting chart

Questionnaire 34-I

Pregnancy week 22

Copy of case notes from hospitals from both groups

Questionnaire 22-F

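### Section 8.2 aims to show no increase in maternal concern but sizes a two-sided difference test with no margin, so a non-significant result could be read as showing no increase

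*Protocol*

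**What the plan says.** Aim and outcome measures (Protocol) makes maternal concern the primary outcome of the second research question, on women's well-being. Section 8.2, Maternal concern, gives the aim: "The goal is to identify no increase in the level of concern in the intervention group".

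The same section takes its mean and SD from an earlier study with the same worry scale; the values "for the survey in pregnancy week 35 were 1.13 (0.65" are per-item means on a 0 to 5 scale. It continues: "Detectable changes are estimated to be a change in mean of 0.12". From this it derives 462 women per arm, at 80% power and a 0.05 level. Whether the test is one- or two-sided is not stated. The value 0.12 is presented as a change that can be detected, not as the largest rise that would be acceptable.

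The introduction to Power analyses describes effects on continuous outcomes by means and standard deviations and names no non-inferiority or equivalence method. Data analyses leaves the choice of methods open and adds: "Participants will be handled according to the intention-to-treat-principle". The planned size of 538 per arm (Sample; section 8.1) comes from the risk-pregnancy outcome.

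The Overview over data collection lists "Mental well-being" at both Survey I and Survey II. I read this as the Cambridge Worry Scale (CWS), the only instrument listed under Maternal well-being.

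**The concern.** The other two primary outcomes aim to show an increase (sections 8.1 and 8.3), and a difference test fits that aim. Only for maternal concern does the desired conclusion coincide with failure to reject the null hypothesis. A non-significant difference does not show that there was no increase. It may only mean that the estimate is imprecise, and attrition or noise makes such a result more likely.

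The background sections ask whether counting is stressful or harmful, and they cite studies in which it raised anxiety. This outcome is where the trial answers that question. Without a limit fixed beforehand, the trial could report no increase while its confidence interval still includes a rise as large as the one it was sized to detect.

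**Working it through.** **Inputs.** Difference 0.12, SD 0.65, 80% power, significance level 0.05 and 462 per arm, all from section 8.2; 538 per arm from Sample and section 8.1. Allocation is taken as 1:1, because each arm has the same stated size and the flowchart specifies "Simple randomization". The margin is not in the Protocol: 0.12 is an assumption below, and other values are shown. No dropout is stated and none is applied.

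**1. Reproduce the Protocol's figure.**

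n per arm = 2 × [SD × (z₀.₉₇₅ + z₀.₈₀) / difference]² = 2 × [0.65 × (1.960 + 0.842) / 0.12]² ≈ 461.

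The two-sample t-test version gives 461.5, which rounds up to 462. A one-sided 0.05 level would give 363. The stated 462 is therefore a two-sided difference calculation.

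**2. Chance of a non-significant result when concern has risen by 0.12.**

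SE = 0.65 × √(2/n), which is 0.0428 at 462 and 0.0396 at 538.

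P(non-significant) ≈ Φ(1.960 − 0.12/SE); the opposite tail is negligible.

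- 462 per arm: Φ(1.960 − 2.806) = 0.199, or 20%.
- 538 per arm: Φ(1.960 − 3.028) = 0.143, or 14%.

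**3. The same true rise under a confidence-limit rule.** Suppose no increase beyond 0.12 is concluded only if the upper limit of the two-sided 95% CI is below 0.12. The chance of that conclusion at a true rise of 0.12 is Φ((0.12 − 0.12)/SE − 1.960) = 0.025 at either size.

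**4. What a borderline non-significant result would leave open.** The largest observed rise that is still non-significant is 1.96 × SE, and its upper 95% limit is twice that.

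| n per arm | Largest non-significant rise | Upper 95% limit |
|---|---|---|
| 462 | 0.084 | 0.168 |
| 538 | 0.078 | 0.155 |

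Both upper limits exceed 0.12.

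**5. Power of the non-inferiority version.** With margin 0.12, true difference 0 and one-sided 0.025, power = Φ(0.12/SE − 1.960).

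- 462 per arm: Φ(0.846) = 0.80.
- 538 per arm: Φ(1.068) = 0.86.

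**6. Sensitivity to the margin** (unadjusted, 80% power, true difference 0):

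| Margin | n per arm |
|---|---|
| 0.08 | 1037 |
| 0.10 | 664 |
| 0.12 | 461 |
| 0.15 | 295 |

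The smallest margin that 538 per arm supports at 80% power is 0.0396 × 2.802 = 0.111. If the true rise were 0.03 rather than 0, a margin of 0.12 would need 819 per arm.

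**7. Baseline adjustment.** ANCOVA multiplies the SE by √(1 − r²), where r is the correlation between the Survey I and Survey II scores. The Protocol does not give r. Over an assumed range of 0.5 to 0.7, power at 538 with margin 0.12 is 94% to 99%. At r = 0.5 the requirement for a margin of 0.10 falls to 664 × 0.75 = 498 per arm.

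**The case against.** - **A reader might infer that the trial will treat a non-significant p-value as proof of safety.** The Protocol does not say so. Data analyses leaves methods open, and a separate analysis plan might contain a confidence-limit rule. This stands, and the point is limited to what could be concluded. It does not remove the mismatch, because section 8.2 itself fixes both the aim and the sizing.
- **The formal research question is neutral.** It asks whether counting affects well-being, and the background allows for effects in either direction and says that some concern may be warranted. A two-sided test suits that question. This stands too, but section 8.2 sets a one-directional aim for the same outcome.
- **A reader might infer that 462 is the wrong number.** It is not. A margin of 0.12 with no true difference requires the same size.
- **Small rises look alarming.** A true rise of 0.06 is non-significant in 71% of trials at 462 per arm and 67% at 538. But such a rise lies inside a margin of 0.12, so under that margin missing it is not a false conclusion.
- **A reader might fault intention-to-treat because non-adherence dilutes a true rise.** Dilution is possible. But the Protocol does not call this the only analysis, and intention-to-treat answers whether all women should be offered a chart. Restricting the analysis to women who counted abandons randomisation. It may also drop women who stopped because counting worried them, which would itself favour finding no increase.

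**Conclusion.** The concern holds as a mismatch between aim and framework in section 8.2. The aim is absence of an increase, the sizing is a two-sided difference test, and the Protocol states neither a margin nor a decision rule. Its size is the gap at a true rise of 0.12: 20% (462 per arm) or 14% (538 per arm) wrongly passed if non-significance is read as no increase, against 2.5% under a confidence-limit rule. These figures assume SD 0.65, 1:1 allocation, no attrition and 0.12 as the relevant limit, which the Protocol does not justify as an acceptable rise.

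The documents do not show that the sample size is wrong, that intention-to-treat is the wrong main analysis, or that the investigators intend to equate non-significance with safety. The point should be fixed, but it does not undermine the design.

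**What to change.** Restate section 8.2 as a non-inferiority objective:

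- Fix and justify the margin on the mean CWS item score before any outcome data are seen. Use 0.12 only if it can be defended as the largest acceptable rise.
- Conclude that there is no increase beyond the margin only if the upper limit of the two-sided 95% CI for the week-34 difference (counting minus control) lies below it.
- Estimate the difference by ANCOVA on the Survey I CWS score.
- Keep intention-to-treat as the main analysis. Label any analysis of women who actually counted as non-randomised and supportive only.
- State the power for the chosen margin, with an allowance for attrition.

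The cost is a rewritten section and a stated decision rule. No new data are needed, because the baseline score is already collected. At a margin of 0.12 and no true difference, the planned 538 per arm is enough before attrition. Below about 0.11 it no longer gives 80% power without baseline adjustment, so the Protocol would need either to justify an assumed correlation or to accept a larger sample.
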